**Figure 2 F2:**
[figure not shown]
Example of label for salt container.

Two staff members of EPHI who are not part of the field study team will receive the salts from the producer and a list of study group assignments from the UC Davis statistician who completes the randomisation list. One of these staff members will place a preprinted adhesive label with the participant ID number and bar code on the container to conceal the letter identifying the type of salt. The second staff member will observe the labelling process and confirm that each participant number is affixed to the correct type of salt. The newly labelled containers of salt will then be stored by participant study number for subsequent distribution.

Project staff members will deliver two containers of the study salts (1 kg salt) to the participating households biweekly for a total of 26 weeks. Any households that use more than the initially delivered amount of salt will be able to request additional salt, as needed. At the time of each home visit for salt delivery, the field workers will request the participants to present their study ID cards to confirm that the correct type of salt is being delivered (by matching the participant identification numbers on the card and the containers of salt). Field staff members will explain repeatedly that: (1) the stored salt should be protected from light and extreme temperatures during storage in the home, and (2) the salt is intended only for consumption by members of the household and should not be shared with other households or used for other purposes.

At the time of each biweekly home visit, the field worker will collect the previously delivered salt containers and any remaining study salt. The field worker will also ask a brief set of questions concerning acceptability of the study salt, use of the salt for special purposes, like preparation of spice mixtures or pickling, use of any other salt (including the amount used and the reason for its use if other salt has been used) and any losses or sharing of the study salt that may have occurred. The leftover salt will be weighed to determine the salt disappearance, which will be expressed both by household and by adult female equivalent based on the theoretical energy requirements of all household members,^33^ considering the household size and composition. During these home visits, the field workers will also check that the women are up to date with regard to their contraception practices and whether they are breastfeeding. Samples of stored salts will be collected at the beginning of the study and every 4 weeks thereafter to analyse the folic acid and iodine concentrations continuously. These results will be monitored over time and will be compared in relation to participant identification number at the end of the trial to confirm correct salt labelling and delivery.

Individual women will participate in the trial for 26 weeks. This period of time has been chosen because it should allow the women to reach a maximum, or near maximum, level of RBC folate concentration following introduction of the intervention, based on the results of a previous supplementation trial.^28^

### Data collection procedures

Within 1 or 2 days of the initial home interviews, potentially eligible, consenting women will be requested to report to one of the local health posts for anthropometric assessment, measurement of blood pressure, fasting blood collection and additional interviews (to determine marital status, birth history, dietary diversity and household food security). The fasting blood specimens (approximately 16 mL whole blood) will be collected for a complete blood count and measurement of RBC folate and serum folate, folate vitamers (including unmetabolised folic acid (UMFA)), homocysteine, vitamin B_12_, methyl malonic acid, thyroglobulin, erythrocyte glutathione reductase activity coefficient, retinol-binding protein (RBP), ferritin, soluble transferrin receptor, C reactive protein, alpha-1-acid glycoprotein, glucose, insulin, genotyping and metabolomics, and to complete a malaria rapid diagnostic test (RDT). Women with a positive malaria RDT will be referred to the local health facility for treatment and will be retained in the study. Blood will be collected again at end line (weeks 24–26 of the intervention) and at a randomly assigned intermediate time point between weeks 4 and 20 of the intervention, using simple random assignment within study arm, such that the blood collections are spread evenly over this interval. (See figure 3 for a summarised schedule of activities.)

**Figure 3 F3:**
[figure not shown]
Schedule of data collection activities for individual study participants. *Blood draw 2 will be completed at a randomly assigned time point between weeks 4 and 20 of the intervention period. At the time of each blood draw, anthropometrics and blood pressure will be assessed. 24-hrUC = 24-hour urine collection to assess urinary iodine and sodium excretion; WFR = weighed food record to assess dietary intake.

All women will participate in dietary assessments—conducted as 24-hour, in-home, weighed food records—to assess discretionary salt intake and will collect 24-hour urine specimens for assessment of urinary iodine and sodium excretion. These studies will be carried out on 1 day before the intervention and 1 day between weeks 4 and 24 of the intervention; a randomly selected subset of 40 women in each study arm will complete these studies a second time during the intervention, 1–2 weeks after the first study, to allow for calculation of intraindividual variation in intakes and urinary excretion.^34^ This is necessary to estimate the distributions of usual discretionary salt intake and urinary sodium and iodine excretion of the study population. Procedures for anthropometry; blood pressure measurement; blood and urine collection, processing and analysis; dietary assessments; and assessments of food security and dietary diversity are described as follows.

#### Anthropometrics

Trained anthropometrists will measure the weight, height, and mid-upper arm, waist and hip circumferences of all women using standard procedures.^35 36^ The results will be expressed as absolute measurements and as body mass index (weight in kilograms/height in metres squared). Weight will be measured in duplicate on a Seca electronic balance (Model 874, Hamburg, Germany) with measurement precision of 0.1 kg. Height will be measured in duplicate using a UNICEF height board (Weigh and Measure; Olney, Maryland, USA), with measurement precision of 0.1 cm. Body circumferences will be measured using flexible, non-stretchable measuring tapes, with measurement precision of 0.1 cm.

#### Blood pressure measurement

Blood pressure will be assessed at the time of the screening interview in the women’s homes and at each of their early morning clinic visits for blood drawing. In particular, following a rest period of at least 15 min while the women are seated, blood pressure will be measured twice at least 3 min apart using an OMRON silver automated blood pressure monitor (OMRON model BP5250). All procedures will adhere to the recommendations of the American Heart Association Council on High Blood Pressure Research.^37^ High blood pressure will be defined as systolic pressure >140 or diastolic pressure >90. If a woman is found to have hypertension during each of the baseline assessments, she will be referred to the local health centre for evaluation and treatment, and she will be excluded from the study.

#### Blood sample collection and processing

On the days of blood collection, eligible women will be requested to arrive at the local health post after fasting for at least 8 hours. Approximately 16 mL blood will be collected aseptically from an antecubital vein by experienced phlebotomists using vacutainer blood collection systems. Collection tubes will be protected from light and processed within 30 min of collection. The resulting specimens will be organised for different laboratory analyses, as illustrated in figure 4. Specifically, 6 mL blood will be collected into a potassium EDTA tube for the malaria diagnostic test; haemolysates for RBC folate determination; and whole blood for a complete blood count, blood smear for morphological examination and preparation of washed RBCs for determination of the erythrocyte glutathione reductase activation coefficient (to assess riboflavin status). The remaining blood will be collected into serum separator tubes and allowed to clot for 30 min (in a cooler and shielded from light). The blood specimens for serum samples will be spun at 3000 g for 10 min at the field site using a portable centrifuge, and the serum will be transferred into multiple cryotubes, as shown in figure 4. All collection and storage tubes will be carefully labelled with preprinted labels containing the participant’s identification number, collection date, type of specimen and a bar code to simplify future identification. One 50 µL serum specimen will be kept in a special, prelabelled tube for shipment to the VitMin Laboratory in Germany, as described below. The storage tubes for folate analyses will be wrapped in aluminium foil to protect them from light exposure, and all tubes except the ones for RBC folate determinations will be transferred immediately to a −20°C freezer at the field site. The samples will be transported to the EPHI laboratory in Addis Ababa in a portable freezer (−20°C) within 1 week. The samples for RBC folate will be processed in the field before freezing, as described below. Once the sample vials arrive at the EPHI laboratory, they will be stored in a freezer at −80°C until laboratory analysis. Each type of specimen (ie, for a particular analysis) will be grouped together in separate storage boxes for easy identification at the time of analysis or shipment to an external laboratory. Samples will be stored until the end of the trial so that all samples from each woman can be analysed together during the same analytical run.

**Figure 4 F4:**
[figure not shown]
Blood collection and processing flow chart. *Second vial for methylmalonic acid (MMA) and metabolomics will be stored at the Ethiopian Public Health Institute (EPHI) in case of loss in transit (two vials of 600 μL to be sent to Texas A&M for MMA and metabolomics). AGP, alpha-1-acid glycoprotein; CBC, complete blood count; CDC, Centers for Disease Control and Prevention; CRP, C reactive protein; EGRac, erythrocyte glutathione reductase activation coefficient; holoTC, holotranscobalamin; RBC, red blood cell; RBP, retinol-binding protein; RDT, rapid diagnostic test; sTfR, soluble transferrin receptor.

#### Twenty-four-hour urine collection, processing and storage

24-hour urine specimens will be initiated during the days of the dietary observations in the participants’ homes using the procedures described for the US National Health and Nutrition Examination Survey.^38^ If the participant is menstruating, the urine collection will be rescheduled. Shortly after the dietitian arrives at the home, the participant will be asked to urinate and discard the urine specimen. The time of that void will be recorded, and all subsequent urine excreted during the next 24 hours will be collected in a plastic bottle by the participant and stored in a cold box provided by the study team. On the following day, the dietitian will return to the participant’s home and request the participant to urinate at the same time that the collection was initiated the previous day. This last specimen will be retained in the collection bottle. The dietitian will then record the time of the final urination, measure the total volume of urine and prepare separate aliquots for transfer to the EPHI laboratory. Samples will be considered acceptable for analysis if the total urine volume is >400 mL, the woman is not menstruating, the collection duration is ≥22 and ≤26 hours and there is no reported loss of any urine specimen during that interval.

#### Dietary intake assessments

Trained data collectors will measure all food and salt intakes during full-day assessments using weighed dietary records collected by direct observation of food preparation and consumption in the participants’ homes. For these studies, the data collectors will arrive at the participants’ homes early in the morning, in time to observe preparation of the first meal of the day. For all meals prepared or consumed during the day, all foods and condiments included in mixed preparations will be weighed to 0.1 g precision before they are added to the cooking pot. The final weight of the completed preparation will be recorded before and after cooking. The amount of each preparation served to the woman and any leftovers will be weighed to calculate the amounts consumed, which will then be expressed as a per cent of the total postcooking weight and multiplied by each raw ingredient weight to determine the amounts of each ingredient that were consumed. Discrete food items, such as pieces of fruit or biscuits, will be weighed separately before serving; any leftovers will be weighed, as described above, to determine the amounts consumed. The data collectors will return to the homes the following day to inquire whether any foods were consumed during the previous night after the dietitian left the home. Any foods consumed during the night (after the last evening meal of the previous day and before the current day’s breakfast meal) will be recorded by recall history using local utensils and the diet balance to estimate the portion sizes. During the same visit, the data collectors will complete the urine collections, as described above.

The total daily consumption of individual foods will be summed and subsequently converted to folate (and other nutrient) intakes using the Ethiopian food composition table (FCT), supplemented with information from the Kenyan, West African, South African, Indian and US Department of Agriculture (USDA) FCTs, as needed. Discretionary salt intake will be measured as all salt (including salt in spice mixtures) added to mixed dishes during preparation or added at the time of consumption. Salt transfer to the preparations or plates will be recorded by weighing the salt storage vessel before and after transfer using a balance with 0.1 g precision.

#### Assessment of household food insecurity and women’s dietary diversity

Household food insecurity will be assessed using the Household Food Insecurity Access Scale published by the US Agency for International Development Food and Nutrition Technical Assistance project.^39^ Household food insecurity will be considered a potential modifying factor for response to folic acid fortification.

The women’s dietary diversity (DD-W) will be assessed using the open recall and recording form suggested by the Food and Agriculture Organization for the 10 food group indicators.^40^ DD-W will be assessed for the previous day at the time of each dietary assessment and at every other salt delivery contact (ie, every 4 weeks). The number of food groups consumed will be averaged for each woman. Minimum dietary diversity will be defined as consumption of at least five food groups, and consumption of leafy green vegetable and legume food groups will be assessed separately and related to folate status.

#### Laboratory analyses

Pregnancy test. A pregnancy test will be completed using a urine dipstick at the time of the screening examination at the local health facility using test materials to be procured through the Ethiopian Ministry of Health.

Malaria RDT. The presence of malaria antigens (*Plasmodium falciparum* and *P. vivax*) in whole blood will be assessed using a drop of blood from the venous blood collection and a point-of-care malaria RDT. The Ethiopian Ministry of Health currently uses the Standard Diagnostics immunochromatographic assay (SD Rapid Test, www.standardia.com).

Haematology assessments. Haematology assessments will comprise a complete blood count and RBC indices, to be completed at the field site using an automated haematology analyser (Sysmex Model XQ-320; Sysmex Europe, Norderstedt, Germany), and a blood film coloured with Wright stain for subsequent microscopic examination, focusing primarily on the presence of hypersegmented polymorphonuclear leucocytes.

RBC folate. RBC folate concentration will be measured at EPHI using a microbiological assay,^41^ as adapted by the US CDC.^42^ For this assay, exactly 100 µL of whole blood collected in EDTA will be diluted in 1 mL 1% ascorbic acid solution (1% weight:volume) to haemolyse the RBCs and maintain folate in a reduced state. The haemolysate will then be promptly frozen and stored at −20°C at the field site until transported to a −80°C freezer at EPHI within 1 week. The microbiological assay of the haemolysate will be performed in quadruplicate using a chloramphenicol-resistant strain of *Lactobacillus rhamnosus* and a 5-methyl-tetrahydrofolate calibrator. Quality control pools for low and high whole blood folate concentration will be analysed with each assay. For each analytical run, a standard growth curve of the organisms will be completed. The growth of the organisms after incubation at 37°C for 42–45 hours will be read as turbidity at 590 nm wavelength using a microplate reader (BioTek Elx808; Agilent, Santa Clara, California, USA). The haematocrit determined on the same blood specimen will be used to calculate the RBC folate concentration.

Serum folate. Serum folate will be measured at EPHI using the same general procedures as described for RBC folate. However, the serum aliquot will be frozen immediately after centrifugation of the blood specimen and will be diluted only after the stored aliquot is thawed for analysis.

Serum homocysteine. Homocysteine will be measured at EPHI on a COBAS 6000 analyser using an enzymatic cycling assay (Roche, reference number 05385415190) that assesses the co-substrate conversion product.

Serum vitamin B_12_ and transcobalamin. Serum vitamin B_12_ and holotranscobalamin will be measured at EPHI on a COBAS 6000 analyser using competitive binding assays (Roche, reference numbers 07212771 and 08717028190).

Serum glucose and insulin. Serum glucose and insulin will be measured at EPHI on a COBAS 6000 analyser using a hexokinase enzymatic method for glucose (Roche, reference number 04404483190) and an electrochemiluminescence immune assay for insulin (Roche, reference number 12017547122). The homeostasis model assessment of insulin resistance (HOMA-IR) will be calculated as described by Matthews *et al*^43^ using the standard ratio formula: HOMA-IR=(FI×FG)/22.5, where FI is fasting serum insulin (pmol/L) and FG is fasting serum glucose (mmol/L).

Serum thyroglobulin. Serum thyroglobulin will be measured at EPHI on a COBAS 6000 analyser using an immunoassay (Roche, reference number 08906556190).

Serum methylmalonic acid (MMA). MMA in serum will be measured at the Texas A&M University Institute for Advancing Health Through Agriculture using the gas chromatography/mass spectrometry (GC/MS) protocol recommended by CDC.^44^ For this assay, MMA is extracted from serum along with an internal standard (d3MMA) using a commercially available strong anion exchange resin. The extracted MMA is derivatised with cyclohexanol to form a dicyclohexyl ester. The derivatised samples are injected onto a gas chromatograph, and the effluents are monitored with a mass detector using selected ion monitoring. Results are quantified by internal calibration using peak area ratios of MMA and the internal standard.

Serum UMFA. Serum UMFA and other folate vitamers will be measured at the Division of Laboratory Sciences, National Center for Environmental Health, US CDC, using isotope dilution liquid chromatography-tandem mass spectrometry according to the method of Fazili *et al*.^45^

Serum RBP, ferritin, soluble transferrin receptor, C reactive protein and alpha-1-acid glycoprotein will be analysed at the VitMin Laboratory in Willstaett, Germany. These specimens will be stored in special tubes provided by the VitMin Laboratory. The samples will be analysed by multiplexed immunoassay, as described previously.^46^ RBP will be expressed in relation to retinol using a regression equation developed during preliminary studies ([name], unpublished).

Metabolomics. Untargeted metabolomics will be completed at Texas A&M University. Serum specimens will be analysed by GC/MS following extraction with methanol and internal standards, followed by derivatisation using methoxyamine hydrochloride and N-methyl-N-trimethylsilyl-trifluoroacetamide, as described by Trezzi *et al*.^47^ Metabolite detection and identification will be performed using MetaboliteDetector software.^48^

Genetic polymorphisms. Analysis of polymorphisms of the genes coding for MTHFR and SHMT1 will be completed at the UC Davis Real-time PCR Research and Diagnostics Core Facility using the methods described previously.^49^ Briefly, DNA will be extracted from whole blood using a QIAcube HT automated nucleic acid work station (Qiagen, Valencia, California) according to the manufacturer’s instructions for the QIAamp 96 DNA QIAcube HT Kit (Qiagen). Quantitative PCR (qPCR) will be completed using the rs1801133 single nucleotide polymorphism (SNP) for MTHFR and the rs1979277 SNP for SHMT1, both of which are available from Thermo Fisher Scientific. The Thermo Fisher Design and Analysis software identifies the genotype based on programmed positives selected before the qPCR analysis is initiated.

Urinary sodium, potassium and iodine. Urinary sodium and potassium concentration will be measured at EPHI on a COBAS 6000 analyser using ion selective electrodes (Roche, reference number ISE NA-U ACN 29071). Urinary iodine concentration will be measured at EPHI using the Sandell-Kolthoff reaction.^50^

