The primary endpoints of the trial are: (1) biweekly disappearance of project-supplied salt from the household; (2) discretionary salt consumption by WRA, as measured by direct observation during in-home weighed food records; (3) changes in markers of folate status (RBC and serum folate, serum homocysteine); (4) changes in markers of iodine intake and status (urinary iodine excretion, serum thyroglobulin); and (5) period prevalence of serious adverse events (SAE). Secondary outcomes include qualitative assessments of salt acceptability, changes in haematological status (haemoglobin (Hb), RBC indices and leucocyte morphology) and possible adverse effects, as assessed from participant reports and by selected metabolic indicators (insulin resistance and metabolomic responses). Possible modifying effects of the intervention that will be explored are: (1) household food insecurity; (2) biomarkers of initial folate, vitamin B_12_ and riboflavin status; and (3) polymorphisms of the genes coding for methylenetetrahydrofolate reductase (MTHFR) and serine hydroxymethyltransferase 1 (SHMT1), which may affect the metabolism of folic acid. We will also assess the effect of free distribution of salt on women’s discretionary salt consumption by monitoring salt intakes and 24-hour urinary sodium excretion before and during the trial.

The study will take place in two rural and two semiurban communities of Gimbichu *woreda*, Oromia Region, Ethiopia (altitude ~2450 m above sea level; figure 1). The total population of the *woreda* is 67 773, of whom ~27% are WRA. According to a preliminary study in the project area, WRA consume a median of 6.6 g discretionary salt per day (95% CI 4.1, 10.2), and, on average, households use approximately 30–47 g salt per day, depending on household size.^25^ A total of 360 eligible women will be randomly assigned to receive one of the three study salts using a block randomisation process.^24^ Based on preliminary studies, salt sharing between households is uncommon, and residents of the study communities are not consuming folic acid-fortified flour ([name], unpublished).

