### Data management and statistical analysis

For most types of data, information will be collected using automated (tablet-based) data entry with range checks and consistency checks incorporated into the data entry software. One exception is the dietary intake data, which will be recorded first on paper forms for preliminary review before entering the consolidated food intake data into the database.

Open Data Kit (ODK) software will be used for primary data collection.^57^ The records will be submitted to a web-accessible ODK aggregate database installed in a dedicated, secure server at EPHI. All sets of up-to-date raw data will be archived in comma-separated value (CSV) format. The archived data will be the aggregated data from each record that formed the basis for editing and analysis. First, all identifiable information will be removed and individual records will be coded just by the participant identification numbers. Deidentified raw data will be retained at EPHI and transferred to UC Davis weekly for editing, generating additional data reports and archiving.

The data managers at EPHI and UC Davis will jointly prepare the data editing syntax, which will be accessible to the appropriate co-investigators, along with the raw data and any data correction forms. Raw CSV data will be exported to STATA V.17 software, and data review and editing will be performed using the same software, for which STATA syntax will be developed. For errors, mistakes or missing data identified during data review, a separate data correction form will be completed and signed by the data collector, supervisor and field coordinator.

A detailed statistical analysis plan will be completed and posted publicly before the analysis is initiated. All study personnel will remain blinded to intervention group assignment (A, B or C) until investigators have reached agreement on result interpretation. Briefly, the data analysis will consist of descriptive analyses of sociodemographic data, anthropometry, blood pressure and vitamin and mineral status at baseline, followed by group-wise comparisons of change in folate and iodine status using both intention-to-treat and per protocol analyses. All data collected from women who subsequently withdraw from the study will be retained and included in the intention-to-treat analyses. Group-wise comparisons of possible adverse metabolic effects will be completed initially just in the control group versus higher folic acid group.

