Variable distributions will be described using means, prevalences and percentiles, as appropriate. Generally, intervention effects will be assessed using analysis of covariance models to estimate group mean differences for continuous outcomes controlling for baseline measurement. Models will be repeated in minimally adjusted and multivariable models to increase the precision of intervention effect estimation. A similar approach will be taken for categorical outcomes using log-binomial or modified Poisson regressions (dependent on model convergence) to estimate prevalence ratios across groups. Prespecified effect modification (eg, by baseline RBC folate concentration, markers of vitamin B_12_ status, genetic polymorphisms and selected household socioeconomic and demographic variables) will be assessed by incorporating interaction terms into the models, followed by regions of significance or stratified analyses to understand the nature of effect modification.

In addition to measuring the impact of the intervention, we will model the levels of folic acid intake necessary to achieve selected RBC folate concentrations. This will be done by using the distribution of RBC folate in the control group to characterise what distribution shift would be necessary to move nearly all (>95%) of the women above the target concentration to minimise the risk of NTDs. Next, the differences in final distributions between the control group and the two intervention groups will be used to interpolate what folic acid fortification level would achieve the desired distribution shift.

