As reviewed in a recent paper on the safety of folic acid fortification,^66^ several expert groups have examined the foregoing concerns regarding possible adverse effects of folic acid supplementation and fortification. These expert groups include the National Toxicology Program of the US National Institute of Environmental Health Sciences,^67^ a National Institutes of Health/FDA/USDA workshop on the metabolic and clinical effects of excess folates/folic acid,^63^ the UK Scientific Advisory Council on Nutrition,^68^ the Norwegian Scientific Committee for Food Safety^69^ and New Zealand’s Office of the Prime Minister’s Chief Science Advisor.^70^ These groups all report that there are no consistent adverse effects of folic acid, and in the few cases where such events have occurred the dose of folic acid that was consumed was considerably greater than what might be provided by a fortification programme. Given the confirmed benefits of folic acid fortification for reducing the risk of NTDs, the unanimous consensus of these groups is that the benefits of folic acid fortification outweigh any unconfirmed potential risks of adverse effects and that folic acid fortification programmes should proceed, while appropriate authorities continue to monitor for any possible adverse effects.

Based on the results of our preliminary studies of 100 women’s discretionary salt intakes in the study communities, we estimate that women in the higher folic acid fortification arm whose usual salt intakes are at the 95th percentile (ie, 10.2 g salt per day) will consume 918 µg folic acid per day from salt.^25^ Thus, the vast majority of women in the study population will consume less than the UL of 1000 µg/day; and we conclude that the proposed level of folic acid fortification should not produce any adverse effects. Nevertheless, we will monitor continuously for any adverse events, and we will assess the women’s insulin sensitivity and metabolic responses to the intervention.

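### The HOMA-IR formula pairs the constant 22.5 with insulin in pmol/L; applied literally, it makes absolute HOMA-IR values and raw mean differences about 6 to 7 times too large

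*Protocol article*

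**What the plan says.** Under Laboratory analyses, in the paragraph on serum glucose and insulin, the protocol article says HOMA-IR will be computed "using the standard ratio formula: HOMA-IR=(FI×FG)/22.5", "where FI is fasting serum insulin (pmol/L) and FG is fasting serum glucose (mmol/L". It attributes the calculation to the original publication of the method. Insulin is to be measured by "an electrochemiluminescence immune assay for insulin (Roche, reference number 12017547122"; the unit in which that assay reports is not given, and no step converting insulin from pmol/L appears there or elsewhere in the article.

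The outcome is secondary. The section on study design, study site and randomisation lists possible adverse effects assessed from participant reports and from "selected metabolic indicators (insulin resistance and metabolomic responses". Safety considerations adds that the study will assess the women's "insulin sensitivity and metabolic responses to the intervention". HOMA-IR is the only index of insulin resistance that the article defines.

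On analysis, Data management and statistical analysis says: "Group-wise comparisons of possible adverse metabolic effects will be completed initially just in the control group versus higher folic acid group". The general method there for continuous outcomes is "analysis of covariance models to estimate group mean differences for continuous outcomes controlling for baseline measurement".

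**The concern.** A normalising constant carries units. In the standard formula, 22.5 scales insulin in µU/mL multiplied by glucose in mmol/L. The article keeps that constant but labels insulin in pmol/L, which gives a number several times larger for the same sample. The constant and the unit cannot both be right.

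The article fixes the formula, the constant and the units itself, so this is a stated inconsistency and not a detail left to the statistical analysis plan. An analyst who codes the sentence as printed would report HOMA-IR means and mean differences on a scale that nobody else uses. That matters because the result is meant to inform whether the higher folic acid level affects insulin resistance. A reader who sets the trial's values beside published ones would see an alarming level that is purely an artefact of units.

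**Working it through.** **Inputs from the article (Laboratory analyses):** divisor 22.5; insulin FI in pmol/L; glucose FG in mmol/L.

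**Inputs not in the article, stated as assumptions:**
- The standard formula sets HOMA-IR to 1 at 5 µU/mL insulin and 4.5 mmol/L glucose (general knowledge of the method).
- The conversion factor *c*, in pmol/L per µU/mL, is taken as 6.0 to 6.945, with an older factor of 7.175 as a sensitivity check.

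**Step 1. Reproduce the constant.** 5 µU/mL × 4.5 mmol/L = 22.5. The article's figure is reproduced with insulin in µU/mL, and not with insulin in pmol/L.

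**Step 2. Divisor needed for pmol/L.** 22.5 × *c*:
- *c* = 6.0: 22.5 × 6.0 = 135.0
- *c* = 6.945: 22.5 × 6.945 = 156.3
- *c* = 7.175: 22.5 × 7.175 = 161.4

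**Step 3. Size of the inflation.** For insulin of *I* µU/mL, the standard value is *I* × FG / 22.5. The formula as printed gives (*c* × *I*) × FG / 22.5. The ratio is *c*, for every woman and every glucose level.

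| Insulin (µU/mL) | Glucose (mmol/L) | Standard value | As printed, *c* = 6.0 | As printed, *c* = 6.945 |
|---|---|---|---|---|
| 5 | 4.5 | 1.00 | 6.00 | 6.95 |
| 8 | 5.0 | 1.78 | 10.67 | 12.35 |
| 12 | 5.0 | 2.67 | 16.00 | 18.52 |

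The insulin and glucose values in this table are illustrative and do not come from the article.

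**Step 4. Reverse check.** As printed, HOMA-IR = 1 at 4.5 mmol/L glucose needs insulin of 22.5 / 4.5 = 5 pmol/L. That is 5 / 6.0 = 0.83 µU/mL or 5 / 6.945 = 0.72 µU/mL, against the reference value of 5 µU/mL.

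**Step 5. What happens to the planned comparison.** Multiplying both the outcome and its baseline by *c* multiplies the adjusted group difference and its standard error by *c*, so the test statistic and p-value do not change. On the log scale, *c* becomes an added constant that the intercept absorbs, so log differences and ratios do not change either.

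A simulated two-group check (100 log-normal values per group, no baseline adjustment) agrees:

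| Multiplier | Raw mean difference | p-value, raw scale | Log-scale difference | p-value, log scale |
|---|---|---|---|---|
| 1 | 0.298 | 0.0097 | 0.150 | 0.0235 |
| 6.0 | 1.79 | 0.0097 | 0.150 | 0.0235 |
| 6.945 | 2.07 | 0.0097 | 0.150 | 0.0235 |

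Only the raw mean difference moves, by exactly the multiplier.

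**The case against.** The strongest answer is that this may be a misprinted unit and nothing more. The article invokes the original method and calls the formula standard. If the laboratory reports insulin in µU/mL, or the analysts follow the cited method, no value will be inflated. This stands as a limit on certainty: the article does not show that wrong values will be produced, only that its own sentence would produce them. It does not remove the mismatch, because the printed unit is explicit.

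A second answer is that the trial's comparative conclusion is safe. The planned analysis compares arms, and a constant multiplier leaves p-values, ratios and log-scale effects as they were. That also stands. The values could be rescaled at any time from the recorded insulin and glucose results. HOMA-IR has no part in the primary endpoints, the sample size, eligibility or the described role of the data and safety monitoring board.

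Third, the basis of 22.5 and the conversion factor lie outside the document. They are therefore labelled as assumptions. No factor in the range considered reconciles 22.5 with pmol/L, since that would need a factor of 1.

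Two stronger readings are tempting, and the article supports neither:
- A reader might infer that nearly all women would be classed as insulin resistant. The article gives no HOMA-IR cut-off and no binary insulin-resistance outcome. Its log-binomial or modified Poisson models are described for categorical outcomes in general and are not assigned to HOMA-IR.
- A reader might infer that the trial's main metabolic safety measure is compromised. The article lists insulin resistance beside metabolomic responses, both as secondary indicators, and ranks neither above the other. Serious adverse events are the primary safety endpoint.

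**Conclusion.** The point holds as a wrong stated formula: the constant 22.5 and insulin in pmol/L do not belong together. If the sentence is followed literally, absolute HOMA-IR values, group means and raw ANCOVA mean differences are too large by a fixed factor of 6.0 to 6.945 (7.175 with the older conversion), and comparison with published HOMA-IR values is invalid. The between-arm inference is not affected.

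This rests on the standard 5 µU/mL × 4.5 mmol/L basis of the constant, on the assumed range for the conversion factor, and on one factor applying to all samples. The last is reasonable, because the article names a single insulin assay at a single laboratory. The severity is minor to moderate: a secondary safety outcome is affected, it can be fully rescaled, and a unit misprint remains possible.

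**What to change.** Confirm with the laboratory the unit in which the insulin assay reports and the conversion factor that applies to it. Then do one of the following:
- state fasting insulin in µU/mL and keep the divisor at 22.5, converting first if the laboratory reports pmol/L; or
- keep fasting insulin in pmol/L and divide by 22.5 times the confirmed factor (135 at 6.0, about 156 at 6.945).

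Use the same unit and divisor in the statistical analysis plan and the analysis code, and check one hand-calculated value against the code's output: 5 µU/mL with 4.5 mmol/L must return 1.0. The cost is one line of text and a check of one line of code. No new data, samples or change to the sample size is needed.
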